**Conclusions:**

Pregnancy monitoring using the REST mobile app is expected to have a significant influence on the number of ANC visits, reduce pregnancy complications, improve normal delivery methods, and ensure the birth weight of the baby stays within normal limits (≥2500 g).

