### Sample Size

The sample size for this study was determined based on the following formula of Lemeshow [19]:

where n is the number of samples per group, Z_1–α/2_=1.96 (at the level of 95% trust), Z_1–β_=0.842 (at 80% power), p_1_ is the proportion of outcomes in the intervention group, p_2_ is the proportion of outcomes in the control group, and p_1_ – p_2_ is the difference between the 2 proportions to be compared.

Based on the calculation of the sample size from previous studies [4,20-22], p_1_=0.92 and p_1_=0.72, so the minimum sample size for the intervention and control groups was 54 respondents each. In cluster RCT research, it is necessary to consider the *design effect* (DE) in determining the sample size. The formula used is DE = 1 + (m – 1), where m=10 (the average number of samples per cluster) and is the intraclass correlation coefficient, assumed to be 0.05.

Based on the calculation results, a DE of 1.45 was obtained. Furthermore, the sample size that was obtained was multiplied by the DE, resulting in a sample size of 78.3, which was rounded to 79 respondents per group. Therefore, the total number of participants needed was 158, although considering a loss to follow-up of ~35% (based on a preliminary study of the attendance of ANC classes in 2019 in Purworejo Regency)*.* Therefore, it was necessary to take a total of 214 (107 participants in the intervention and the control group each) at the beginning of the study through cluster sampling. The number of clusters to be used was 22 groups of pregnant women, so each group needed 9.72 samples, rounded 10 pregnant women in each group.

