#### Primary Outcomes

##### Pregnancy Complications

Pregnancy monitoring using the mobile REST mobile app can prevent complications during a mother’s pregnancy compared to not using the app. Once the trial began, the definition of primary results was refined from “pregnancy complications” to “specific conditions of complications experienced by the mother during pregnancy, such as anemia, hypertension, and chronic energy deficiency.” These changes were made before data analysis and have been documented in the protocol.

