### Data Analysis

Descriptive statistics were used to find out the basic characteristics of the entire study group. For bivariable analysis, the independent *t* test or Mann-Whitney U test, and the chi-square test or the Fisher precise test were applied for categorical results, adjusting for group design, if necessary.

Multivariable analysis was performed using mixed effects models to account for clustering at the level of the ANC class cluster. A mixed effects linear regression model was used for sustained outcomes, such as the number of ANC visits and birth weight. Mixed effects logistic regression models were used for binary outcomes, such as pregnancy complications and delivery methods. All models included random interception to account for variations between clusters and fixed effects for interventions, as well as potential confounding variables, including maternal age, education level, socioeconomic status, obstetric history, and nutritional status. Statistical significance was determined using a 2-headed *P* value of <.05.

For each primary and secondary outcome, we used an estimate of the effect size and its precision (95% CIs). Other analyses, including subgroup analysis and customized analysis, of study results were also carried out. Stata 14.0 was used to analyze the data.

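### Four unranked primary outcomes are each tested at two-sided .05 with no success rule; separately, the 80% power is tied to none of them

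*Protocol article*

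**What the plan says.** Under the heading "Primary Outcomes" the protocol article sets out four outcomes: pregnancy complications, methods of delivery, birth weight and ANC visits. None is ranked or singled out.

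The Data Analysis section gives each outcome a model. ANC visits and birth weight get a mixed effects linear regression; complications and delivery method get a mixed effects logistic regression. It then states one general rule: "Statistical significance was determined using a 2-headed" P value below .05. It gives no testing order, alpha split or adjustment, and does not say whether one success or all four are needed.

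The Sample Size section has a single two-proportion calculation, with "Z_1–α/2_=1.96 (at the level of 95% trust") and "Z_1–β_=0.842 (at 80% power"). The rates are printed as "p_1_=0.92 and p_1_=0.72" (the second is evidently p2), "so the minimum sample size for the intervention and control groups was 54 respondents each". They are drawn from earlier studies and described only as proportions of outcomes. Which of the four outcomes they belong to is not stated.

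The Conclusions of the Abstract say that monitoring with the app "is expected to have a significant influence on the number of ANC visits, reduce pregnancy complications, improve normal delivery methods" and keep birth weight within normal limits.

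**The concern.** Two separate problems arise.

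The first is type I error. With four unranked primary outcomes, each judged at .05, nothing in the article stops a single significant result from being reported as a positive primary finding. Under that use, the 5% describes each test but not the trial's overall chance of a false positive primary claim.

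The second is power. The 80% was calculated for one contrast that the reader cannot match to any of the four outcomes. Two of them are analysed as continuous variables, and a difference between two proportions does not describe those tests. A reader may still take the 80% as covering the primary set.

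The Conclusion of the article already recommends integrating the app into national programmes, so what counts as a positive primary result matters.

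**Working it through.** **Inputs from the article.** Four primary outcomes (Primary Outcomes); two-sided .05 for each (Data Analysis); z values 1.96 and 0.842, rates 0.92 and 0.72, cluster size m = 10, intraclass correlation 0.05 (Sample Size). **Assumed:** the correlation between the four test statistics, which the article does not give. I take an equal pairwise correlation r from 0 to 0.9.

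**Step 1. Reproduce the plan's sample size.** The unpooled two-proportion formula is n = (z_α + z_β)² × [p1(1−p1) + p2(1−p2)] / (p1−p2)².

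- Variance terms: 0.92 × 0.08 + 0.72 × 0.28 = 0.0736 + 0.2016 = 0.2752.
- n = (1.96 + 0.842)² × 0.2752 / 0.20² = 7.851 × 0.2752 / 0.04 = 54.02, which matches the stated 54. The pooled version gives 57, so the unpooled form is evidently the one used.
- Design effect: 1 + 9 × 0.05 = 1.45; 54 × 1.45 = 78.3, stated as 79 per group.

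The calculation reproduces, but it is for one test at .05.

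**Step 2. Familywise error for four tests at .05.** This supposes that all four null hypotheses are true and that any one significant result counts as success.

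- Independent: 1 − 0.95⁴ = 0.185.
- Correlated: simulation of four equicorrelated normal test statistics, two million draws for each r.

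| r | Familywise error |
|---|---|
| 0 | 18.5% |
| 0.1 | 18.4% |
| 0.2 | 18.1% |
| 0.3 | 17.4% |
| 0.4 | 16.6% |
| 0.5 | 15.6% |
| 0.6 | 14.4% |
| 0.7 | 13.0% |
| 0.8 | 11.4% |
| 0.9 | 9.4% |

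The rate is 15-19% up to a correlation of roughly 0.5 and falls below 15% a little above that. At 0.9 it is still nearly twice 5%.

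**Step 3. Error at the adjusted level.** The strictest Holm step is 0.05/4 = 0.0125. Four independent tests at that level give 1 − 0.9875⁴ = 4.9%. Holm keeps the familywise error at or below 5% under any correlation.

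**Step 4. Power for the planned contrast at .0125.** On the same normal-based formula, with 54 effective participants per arm:

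- Standardised difference: 0.20 / √(0.2752/54) = 2.80.
- Critical value at two-sided .0125: 2.498.
- Power = Φ(2.80 − 2.498) = Φ(0.30) ≈ 0.62.

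This is a lower bound under Holm, because an outcome that is not the smallest P value may be tested at a later, looser step.

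**The case against.** The strongest objection is that the article states no any-one-succeeds rule. The Abstract and the hypothesis under Strengths and Limitations list the benefits jointly. If all four had to reach significance, the type I error would not be inflated. This stands as a condition on the figure: a reader might infer that the trial's false positive rate simply is 15-19%, and the article does not support that without the condition. It does not remove the point, because the joint wording is a statement of expectation, not a decision rule. Under an all-four rule the 80% still would not be the power to succeed.

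A second objection is that multiplicity is often left to an analysis plan, and this is a condensed article. That would answer silence. Here the article itself fixes the threshold and applies it to four unranked primary outcomes.

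Three further readings are tempting but not supported:

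- That the unidentified outcome behind the power calculation causes the error inflation. It does not. The inflation comes from four tests at .05; the unidentified outcome is a power problem only.
- That anemia, hypertension and chronic energy deficiency are tested separately, giving six primary tests. They are named as examples of complications, but Data Analysis treats complications as a binary outcome and no section announces three tests.
- That power for birth weight can be worked out from low-birth-weight rates. The article gives no such rates, and it models birth weight linearly.

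**Conclusion.** The point holds in two separate parts. First, four unranked primary outcomes at two-sided .05 give a familywise error of about 15-19%, not 5%. This rests on three assumptions: all four nulls are true, any one significant result may be claimed, and the test statistics correlate at no more than about 0.5. At a correlation of 0.9 the figure is about 9%. Second, the 80% power belongs to a single contrast of proportions with no named outcome and cannot be read as power for the primary set. Both are faults in what the article fixes, and both can be repaired without new data.

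**What to change.** **Error control.** Apply Holm across the four primary outcomes at overall two-sided 5%, with ordered thresholds .0125, .0167, .025 and .05. Use one P value per outcome, from the mixed effects model that Data Analysis assigns to it, with complications as the binary outcome already given there. The Abstract dates the analysis to April 2025, so label the correction as added after the analysis and show the unadjusted P values beside the adjusted ones. Holm avoids picking a single primary outcome at this stage.

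**Power statement.** Name the outcome behind 0.92 and 0.72 and limit the 80% to that outcome at .05. State that its power at the strictest Holm step (.0125) is about 62% on the article's own normal-based formula, a lower bound under Holm. State that the other three outcomes have no power calculation.

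**Cost.** Wording and a re-reading of existing P values; no new participants or data. The downsides are a stricter threshold for the smallest P value and a less favourable power figure.

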### Data Management

The data collected will be kept confidential for the duration of the study and disposed of after a period of 5 years. The data collection process from the beginning to the end of the study used 2 different methods. In the control group, data were collected using a form that was transcribed into electronic format, and in the intervention group, data were collected using an app and transcribed into electronic format that was stored on a desktop computer. These stored data will be used for further analysis. The individual appointed as the chair of the student project committee at the institute is responsible for overseeing data management.

To address missing or incomplete data, the researchers implemented proactive data validation and monitoring procedures within the REST mobile app. Real-time data entry validation rules were embedded in the app to minimize input errors and prevent incomplete submissions. In cases where data were missing or inconsistencies were detected, follow-up verification was conducted by the research team through direct contact with the respective participants or midwives, as appropriate. For statistical analysis, missing data will be assessed for patterns and mechanisms. Depending on the extent and nature of the missing data, appropriate methods, such as multiple imputation or complete-case analysis, will be used. To ensure overall data quality and accuracy, regular data audits will be performed, and all electronic data will be stored in secure, access-controlled databases with audit trails. These procedures have been designed to enhance data integrity and minimize bias due to incomplete or inaccurate information.

## Results

In July 2023, the REST mobile app was prepared and tested in small community groups, including midwives and pregnant women, through simulation. In September 2023, the app was further developed and refined based on the feedback from these small group trials and then introduced to study participants. A total of 22 ANC class clusters were involved, comprising 22 midwives and 220 pregnant women in Purworejo Regency. These were divided into 2 groups: 11 (50%) intervention clusters using the REST mobile app and 11 (50%) control clusters. The majority of participating pregnant women were aged 20-35 years (n=168, 76.4%), consistent with national demographic trends. Approximately 185 (84.1%) had secondary education (junior and senior high school), and 57 (25.9%) had tertiary education (college graduates). The participants were evenly distributed across economic quintiles, reflecting diverse socioeconomic backgrounds, and most lived approximately 1 km from a health facility.

To provide a clearer overview of both completed and planned study phases, Table 4 presents the planned timeline for each phase of the RCT.

**Table 4 table4:** Planned timeline^a^ for study phases.

Phase	Start	End
Ethical approval	April 2023	April 2024
Staff training/preparation	July 2023	October 2023
Participant recruitment	November 2023	January 2024
Intervention implementation	February 2024	July 2024
Follow-up/data collection	August 2024	February 2025
Data analysis	March 2025	June 2025
Report writing/publication	July 2025	December 2025

^a^Dates are tentative and may be adjusted based on field conditions and recruitment outcomes.

## Discussion

### Summary

The advantages of using mobile apps for pregnancy monitoring vary from app to app as each app provides different features. The results of previous studies related to the use of mobile apps for pregnancy monitoring are considered effective and are grouped into 4 categories:

Apps that provide information (eg, the Health Gestation app and CHAT). This app provides information that pregnant women need to monitor their pregnancy [4,27].Apps used to conduct counseling between midwives and pregnant women through text messages and a voucher component [28].Apps that help pregnant women make decisions and provide them with mental support (eg, the Quantitative Innovation in Predicting Preterm Birth [QUiPP] app and SP^+^ [16,29].Apps that help pregnant women in managing during their pregnancy (eg, the ImTeCHO health assistant app). This app helps pregnant women perform self-monitoring and understand the condition of pregnancy well [10,30,31].

The REST mobile app is the first app designed to be used by midwives and pregnant women in which the data input by the midwives and pregnant women will be integrated. This app can also be used for comprehensive maternal health monitoring. This study used a cluster RCT design with the hope that the group comparison will be used as a benchmark for the effectiveness of using the REST mobile app.

Evidence from RCTs and systematic reviews indicates that mobile-based reminders and educational messaging can significantly increase ANC class attendance, facility-based deliveries, and maternal knowledge. For example, a cluster RCT in Zanzibar [28] demonstrated that mobile health (mHealth) interventions increased the proportion of women attending 4 or more ANC visits from 31% to 44%. Systematic reviews [32,33] further support these findings, confirming that mHealth tools enhance the uptake of maternal and newborn health services. However, although intermediate outcomes have improved, direct evidence showing a significant reduction in maternal mortality through mHealth interventions remains limited. This is largely due to the rarity of maternal deaths and the need for large sample sizes to detect such effects statistically. Despite this, by strengthening maternal health care behaviors and improving access to services, mobile apps like REST are likely to contribute indirectly to the reduction in maternal and neonatal mortality over time.

The risk identification component of the REST mobile app involves midwives identifying risks from the results of the ANC examination. Evaluation counseling involves app-based counseling from midwives for pregnant women, which makes it easier for pregnant women to make decisions. Systematic monitoring by midwives focusing on 10T includes measuring the weight and height (T1), blood pressure (T2), mid-upper arm circumference (T3), uterine fundal height (T4), tetanus immunization (T5), iron supplement tablets (T6), fetal presentation and fetal heart rate (T7), counseling (including childbirth and postpartum preparation; T8), hemoglobin levels (T9), and providing care as needed (T10) [5]. Troubleshooting involves midwives determining solutions to problems faced by pregnant women in their group.

Although the current version of the REST mobile app is limited to ANC, future development phases aim to expand its functionality to include postpartum and early childhood monitoring. Planned features include digital tools for recording postnatal visits, maternal well-being assessments, breastfeeding tracking, and early detection of postpartum complications. For child monitoring, key components will include vaccination tracking, child growth chart integration, and developmental milestone assessments based on national pediatric guidelines. This expanded scope will support a continuum-of-care approach and further strengthen maternal and child health outcomes through sustained digital engagement beyond pregnancy.

### Strengths and Limitations

We hypothesize that the intervention will result in improvements in the number of ANC visits, a reduction in pregnancy complications, and improved delivery outcomes in the intervention group. However, this study has several limitations typical of eHealth trials. As this study used a cluster RCT design, potential biases, such as selection bias, limited comparability between clusters, and residual confounding despite adjustment, may have influenced the observed effects. Therefore, although the REST mobile app shows promise in supporting maternal health, causality cannot be definitively established, and further research may be needed to confirm these findings in other settings. Next, due to the nature of the intervention, participants could not be blinded, which may have introduced performance and reporting bias. Not all participants used the intervention as intended, revealing challenges related to usability and compliance in digital health trials. Additionally, varying internet access across regions posed a challenge in ensuring consistent results across health app trials. Although a mixed effects model was used to adjust for confounding, unmeasured factors may still contribute to residual confounding. Loss to follow-up could lead to attrition bias if it differs systematically between groups. Lastly, the findings may not be fully generalizable to all pregnant women in Indonesia or other low-resource settings due to the specific characteristics of the study sites and participants.

The REST mobile app installation process must be through a website [26], as the app is not yet available on App Store or Google Play Store. Its use is still limited to the research area, namely Purworejo Regency (Central Java, Indonesia). The output of the research is expected to have an effect on improving maternal and child health, and the app will be further developed more widely to reach national and global levels.

### Conclusion

The cluster RCT study on the use of the REST mobile app aims to compare the welfare of pregnant women. The app used by midwives and pregnant women in the intervention group will help monitor the activities of ANC classes that are routinely carried out by the public health centers. The control group that did not use the app carried out class activities for pregnant women in accordance with implementation standards.

The study highlights the potential of the REST mobile app to enhance maternal health services in rural Indonesia by supporting early risk detection, improving service use, and empowering women through health education. Integration into national health programs is recommended. Findings will be disseminated to local stakeholders through presentations and simplified reports and to national policymakers, professional bodies, and the research community via publications, conferences, and open access platforms.

## Appendix

Multimedia Appendix 1 CONSORT-eHEALTH checklist (V 1.6.1).

Multimedia Appendix 2 Fillable SPIRIT Outcomes 2022 checklist, along with the SPIRIT 2013 checklist.

## Abbreviations

ANC: antenatal care
CONSORT: Consolidated Standards of Reporting Trials
DE: design effect
ImTeCHO: Innovative Mobile Phone Technology for Community Health Operations
mHealth: mobile health
MMR: maternal mortality rate
RCT: randomized controlled trial
REST: Risk Identification, Evaluation Counseling, Systematic Monitoring, Troubleshooting
SPIRIT: Standard Protocol Items: Recommendations for Interventional Trials
TIDieR: Template for Intervention Description and Replication
WHO: World Health Organization
